### 2.2. Pilot Trial Justification

Feasibility studies are recommended prior to conducting definitive randomized controlled trials to assess whether an intervention can be successfully implemented in real-world settings [14]. Such studies help identify potential issues related to participant recruitment, adherence, intervention delivery, and outcome measurement, which may influence the success of larger-scale trials.

In the context of exercise interventions among college students, feasibility studies are particularly important due to potential barriers such as academic schedules, time constraints, and variability in exercise adherence. The present study therefore aims to evaluate the practicality, acceptability, and preliminary effectiveness of a time-specific HIIT programme for Chinese college students. Findings from this pilot trial will inform the refinement of the intervention protocol and support the design of a future fully powered randomized controlled trial.

### 2.3. Sample Size

Sample size estimation for the pilot trial was guided by the recommendations of Whitehead et al., [15] for pilot randomized trials. These recommendations indicate that pilot studies should recruit sufficient participants to provide preliminary estimates of effect size that can inform the sample size calculation for a subsequent definitive trial.

Based on these guidelines, approximately 15–25 participants per group are considered adequate for pilot trials investigating continuous outcomes with moderate effect sizes. Therefore, the present study aims to recruit approximately 72 participants in total, with 24 participants allocated to each study group (morning HIIT, evening HIIT, and control).

For the qualitative component, interview-based studies typically achieve data saturation with 9–17 participants [16]. Therefore, approximately 10–15 participants will be purposively selected for interviews. Additional interviews will be conducted if new themes continue to emerge during analysis.

### 2.4. Eligibility Criteria

Participants will be recruited from full-time undergraduate students enrolled at Qiqihar University. To be eligible for inclusion, participants must be full-time undergraduate students at Qiqihar University, classified as having an intermediate chronotype as determined by the Chinese version of the Morningness–Eveningness Questionnaire (MEQ) [17], and identified as having low physical activity levels (<600 MET-min/week) based on the short form of the International Physical Activity Questionnaire (IPAQ) [18]. Both the Chinese version of the MEQ (Cronbach’s α= 0.769) and the IPAQ-SF (Cronbach’s α = 0.82) are widely used instruments that have demonstrated acceptable reliability and validity in Chinese populations and have been extensively applied in health- and physical activity-related research.

Participants will be excluded if they are unable to safely participate in physical activity, have clinically diagnosed mental disorders, musculoskeletal or cardiovascular conditions that contraindicate high-intensity exercise participation, or are unable to provide informed consent. Prior to participation, all eligible participants will undergo basic health screening to ensure the safety and appropriateness of participation in the HIIT intervention programme.

### 2.5. Recruitment Procedures

Participants will be recruited through announcements distributed across the university campus. Interested students will first complete screening questionnaires including the MEQ and IPAQ. MEQ scores between 42 and 58 will classify participants as having an intermediate chronotype, while IPAQ scores below 600 MET-min/week will indicate low physical activity levels. Students meeting both criteria will be invited to participate in the study.

### 2.6. Randomization and Allocation

Eligible participants will be randomly assigned to one of three groups: Morning HIIT, Evening HIIT, or Control group, using a restricted lottery-based randomisation method with a 1:1:1 allocation ratio. To generate the allocation sequence, a total of 72 identical opaque sealed envelopes will be prepared, comprising 24 envelopes labelled “Morning HIIT”, 24 envelopes labelled “Evening HIIT”, and 24 envelopes labelled “Control”. The envelopes will be identical in size, colour, and appearance, and each allocation label will be folded and sealed inside the envelope so that the assignment cannot be seen before selection.

To ensure allocation concealment, the envelopes will be prepared and mixed by an independent researcher who is not involved in participant recruitment, baseline assessment, intervention delivery, or outcome assessment. The sealed envelopes will be placed in an opaque container and thoroughly mixed before the allocation process begins. Randomisation will be conducted only after eligibility confirmation, written informed consent, and completion of baseline assessments.

At the point of allocation, each participant will independently draw one sealed envelope from the opaque container under the supervision of a research team member. The selected envelope will then be opened to reveal the participant’s group assignment. Once selected, the envelope will not be returned to the container. This lottery procedure will be conducted without replacement until the required allocation of 24 participants per group is achieved. This process ensures that each participant’s allocation is concealed before assignment and is made independently and unpredictably upon enrolment.

Participants allocated to the Morning HIIT group will perform the training sessions in the morning, whereas participants allocated to the Evening HIIT group will perform identical training sessions in the evening. Participants allocated to the Control group will maintain their usual daily routines without participating in structured exercise during the study period. A schematic CONSORT diagram illustrating the intervention procedure is shown in Figure 2. Table 1 outlines the participant recruitment timeline, key milestones, and planned assessment activities.

### 2.7. Intervention

#### Chrono-HIIT Exercise Intervention Protocol

The Chrono-HIIT intervention programme was developed specifically for college student populations, taking into consideration their general fitness levels, feasibility within a college setting, and the need for a time-efficient exercise strategy. The programme is designed as a short-duration body weight high-intensity interval training (HIIT) session that can be performed without specialised equipment. Each training session comprises three sequential phases: warm-up, HIIT, and cool-down, with a total session duration of approximately 10 min.

*Warm-up Phase*

A structured warm-up is performed at the beginning of each session to prepare the musculoskeletal and cardiovascular systems for subsequent high-intensity activity and to reduce the risk of exercise-related injury [19]. Participants will begin with 60 s of light jogging in place, which gradually elevates heart rate and increases blood circulation to the working muscles.

This will be followed by dynamic stretching exercises involving both upper and lower extremities, including movements targeting the shoulders, trunk, hips, and lower limbs. These dynamic movements are intended to improve joint mobility, enhance neuromuscular activation, and ensure physiological readiness before commencing the high-intensity exercise phase.

*HIIT Phase*

The HIIT component consists of eight simple body-weight movements designed to be easily performed by college students without specialised equipment. The total duration of the HIIT phase is approximately 8 min, with exercises performed in repeated high-intensity bouts interspersed with brief recovery periods. The detailed exercise protocol, including the sequence of movements and interval duration, is presented in Table 2.

Exercise intensity during the HIIT phase will target approximately 80–90% of the participants’ age-predicted maximum heart rate (HRmax), which is consistent with recommended intensity ranges for high-intensity interval training in young adults. Estimated HRmax will be calculated using the age-predicted formula: HRmax = 220-age [20]. Prior to the intervention, the principal investigator will provide standardised demonstrations of all exercise movements to ensure correct technique and consistency across participants. Training sessions will only begin once participants confirm their understanding of the exercises and demonstrate the ability to perform them safely and correctly.

To ensure intervention fidelity and adherence, attendance will be recorded for each training session. Participants will also be verbally encouraged to maintain the required exercise intensity during the intervals. Any adverse events, discomfort, or injuries occurring during the training sessions will be documented and monitored throughout the intervention period to ensure participant safety.

*Cool-down Phase*

Following completion of the HIIT session, participants will perform a brief cool-down phase consisting of relaxation exercises and static stretching. The primary aim of the cool-down is to gradually reduce cardiovascular demand and facilitate physiological recovery after high-intensity activity [21].

The cool-down routine includes static stretching exercises targeting the major muscle groups involved during the training session, particularly the lower extremities and upper body. These stretches help relieve muscle tension, restore normal muscle length, and improve flexibility following vigorous exercise [22].

Overall, the cool-down phase is designed to promote post-exercise recovery and minimise the likelihood of delayed onset muscle soreness or exercise-related discomfort.

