### 2.8. Exercise Intensity Monitoring

Exercise intensity will be monitored using both objective and subjective measures. For an objective measure, participants will wear heart rate monitoring wristbands during all training sessions. Exercise intensity will be maintained at approximately 80–90% of estimated maximal heart rate (HRmax). While for subjective measure, participants will also rate their perceived exertion using the modified Borg Rating of Perceived Exertion (RPE) scale (0–10) immediately after each training session.

Given that the study involves participants with low prior physical activity levels, safety monitoring will be conducted throughout the intervention period. Before each training session, participants will be asked about their current physical condition, including any musculoskeletal pain, illness, dizziness, unusual fatigue, or other symptoms that may affect safe participation. During each session, the principal investigator or trained research personnel will observe participants for signs of exercise intolerance, including excessive breathlessness, dizziness, chest discomfort, nausea, musculoskeletal pain, or inability to maintain correct movement technique. Participants will be instructed to stop exercising immediately if they experience any concerning symptoms.

All adverse events and safety-related incidents will be documented using a standardized adverse event recording form. Information recorded will include the type of event, timing, severity, relationship to the intervention, action taken, and outcome. Serious adverse events, if any, will be reported to the research team and relevant ethics committee in accordance with institutional requirements.

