### 2.9. Outcome Measure

#### 2.9.1. Feasibility Outcomes

The primary outcomes of the study are feasibility indicators, including recruitment rate, retention rate, adherence rate and data missing rate. Recruitment will be considered successful if more than 70% of eligible students agree to participate. Retention will be considered acceptable if more than 80% of participants complete the intervention. Adherence will be defined as participation in more than 70% of the prescribed training sessions. To account for partial participation, adherence will also be calculated as the proportion of completed training sessions relative to the total number of prescribed sessions. Participants who attend some, but not all, scheduled sessions will therefore be categorized according to their overall attendance percentage. The overall missing data rate is expected to remain below 10% [23,24]. Feasibility thresholds were established based on recommendations for pilot and feasibility trials and commonly used progression criteria in feasibility research [25].

Safety-related outcomes will include the number, type, severity, and relatedness of adverse events occurring during the intervention period. Adverse events will include any undesirable physical or psychological symptoms occurring during or after the HIIT sessions, such as musculoskeletal pain, dizziness, excessive fatigue, nausea, shortness of breath beyond expected exertion, or injury. Events will be categorized as mild, moderate, or severe, and as unrelated, possibly related, or probably related to the intervention. These safety indicators will be used to evaluate whether the Chrono-HIIT programme can be delivered safely among college students with low prior physical activity levels.

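### The adverse-event window is worded in different ways and the described checks depend on attendance, so some events in the HIIT arms may go unrecorded

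*Protocol article*

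**What the plan says.** The protocol article describes the adverse-event window in three places.

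- Section 2.7, in the paragraph on fidelity and attendance: "Any adverse events, discomfort, or injuries occurring during the training sessions will be documented and monitored throughout the intervention period".
- Section 2.9.1, as the definition: "Adverse events will include any undesirable physical or psychological symptoms occurring during or after the HIIT sessions".
- Section 2.9.1, as the outcome: "Safety-related outcomes will include the number, type, severity, and relatedness of adverse events occurring during the intervention period".

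Section 2.8 describes how events come to light. One step is a question: "Before each training session, participants will be asked about their current physical condition, including any musculoskeletal pain, illness, dizziness, unusual fatigue", together with other symptoms that could make taking part unsafe. The other is staff observation: "During each session, the principal investigator or trained research personnel will observe participants for signs of exercise intolerance". The section also states in general terms that "safety monitoring will be conducted throughout the intervention period" and that every adverse event goes on a standard form.

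The Introduction lists safety within the primary objective. Section 2.9.1 says the safety indicators will be used to judge whether the programme can be delivered safely to students with low prior activity. The Discussion relies on the same monitoring before a larger trial is started.

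**The concern.** A safety result is only as good as the route by which events reach the form. Here the outcome covers the whole intervention period, but the two described routes operate only when a participant comes to a session. An event that keeps someone away also takes that person out of reach of both checks. Under-recording would then be related to harm rather than random, and it would act in the direction that favours the programme.

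Delayed effects are not remote in this setting. The cool-down text in Section 2.7 says that phase is meant to "minimise the likelihood of delayed onset muscle soreness or exercise-related discomfort", so the plan itself expects symptoms that appear after the session has ended.

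At stake is the judgement on safe delivery, which is part of the primary objective and feeds the decision on a definitive trial.

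**Working it through.** The plan gives no figure to reproduce here. The check is a comparison of the text, followed by two counts and a statement of direction.

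**1. The windows side by side.** Take knee pain first felt the day after a session. Section 2.7 does not name it, because its sentence speaks of events within sessions. The definition in Section 2.9.1 includes it. The outcome sentence in Section 2.9.1 includes it if the day lies in the intervention period. For an event after the last session, the definition still applies with no end point. Whether the outcome sentence applies depends on when the intervention period ends, which is not said.

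**2. Which described step reaches which event.**

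| Event | In-session observation | Pre-session question | Any other described step |
|---|---|---|---|
| Shows during an attended session | Yes | Not needed | Not needed |
| Starts between sessions, still present at the next attended one | Possibly | Yes, but entry on the form is not stated | Not needed |
| Starts between sessions, cleared by the next one | No | Not as worded, since it asks about present condition | None |
| Causes missed sessions, participant later returns | No | Only if still present on return | Strength-test screen at Week 8, if still present |
| Leads to withdrawal | No | No | Strength-test screen only if the person returns for testing |
| Starts after the last session | No | No | Strength-test screen, if testing follows that session |

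The strength-test screen is the check for musculoskeletal contraindications before maximal strength testing (Section 2.9.2). Table 1 schedules the fitness tests at allocation and again at Week 8. The screen is not linked to the adverse event form, and its order relative to the last session is not given. The interviews do not reach people who withdrew, because Section 2.1 samples completers.

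**3. How much absence the plan's own criteria allow.**

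- Sessions: 3 per week × 8 weeks = 24 (Abstract). Adherence needs more than 70% (Section 2.9.1): 0.70 × 24 = 16.8, so at least 17. An adherent participant may miss 24 − 17 = 7 sessions.
- Retention needs more than 80% of participants (Section 2.9.1), with 72 planned (Section 2.3): 0.80 × 72 = 57.6, so at least 58 (58/72 = 80.6%). Up to 72 − 58 = 14 may be lost, over all three groups, with retention still acceptable.

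These are limits on absence. They are not estimates of the number injured or the number of events missed.

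**4. Direction.** Expected recorded events = Σ (true events of type k × capture probability c_k), with each c_k between 0 and 1. Spurious entries aside, the recorded count cannot exceed the true count, and it equals it only if every c_k is 1. If injury raises the chance of absence, c_k is lower for the events that matter most, so the recorded rate is pulled down. The documents give no value for any c_k, so no size can be calculated.

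**The case against.** The strongest reply is that the sentence in Section 2.7 describes a subset. It says events in sessions will be documented and does not say that only those will be. Read with the definition in Section 2.9.1 and the promise in Section 2.8 that all adverse events go on the form, a later event is already reportable. This stands as to intent: the difference is loose wording, not a rule of exclusion. It does not supply a step that would find such events.

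A reader might infer more than the text supports:

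- **That delayed or absence-causing injuries certainly go unrecorded.** With three sessions a week, a symptom still present at the next attended session falls under the pre-session question, and nothing rules out self-report.
- **That nothing is asked after the last session.** The screen before strength testing, repeated with the Week 8 assessment, is a possible later check, although a partial one.
- **That the loss can be sized by treating every permitted dropout as an unrecorded injury, or by the small share of the eight weeks spent under observation.** The first is an invented scenario. The second ignores the pre-session question.
- **That a morning-versus-evening safety comparison could reverse.** The plan specifies no such comparison. Section 2.12 summarises safety descriptively, and the morning-versus-evening objective in the Introduction concerns fitness.

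Two further points have weight. Withdrawals through injury would still lower retention, so the harm would not be wholly invisible. And this is a condensed article: contact with absentees and the exact question may be set out in a full protocol that is not shown. The inconsistent windows and the framing of the question around present condition are, however, stated here.

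**Conclusion.** The point holds in a limited form. The window is worded inconsistently and has no stated end, and the collection steps described do not fully deliver the safety outcome stated. Events that resolve between sessions, events behind absence or withdrawal, and events after the last session may be missed.

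The likely effect is a downward bias in the observed adverse-event rate in the HIIT arms. Its size is unknown and could be small. This conclusion assumes that the described steps are the main ones and that some events in this population lead to absence. If the full protocol already follows up absentees and withdrawals, what remains is the wording of the window and of the question.

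This should be corrected because safety is in the primary objective and the change is cheap. It does not invalidate the design.

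**What to change.** These changes affect recording only and leave clinical management untouched.

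1. Reconcile Sections 2.7 and 2.9.1 to one window for the HIIT arms, from the first session through the Week 8 assessment. Define the intervention period in Section 2.9.1 to match. State that the Week 8 question is put after the participant's last session, since Table 1 places both in the same week without an order.
2. Word the pre-session question in Section 2.8 to cover the time since the last session as well as present condition, and state that positive answers are entered on the adverse event form.
3. For each missed session and each withdrawal, send a short standard message that records the reason and asks whether a symptom or injury occurred.
4. Ask the same question once at the Week 8 assessment, alongside the musculoskeletal screen in Section 2.9.2, and enter positive answers from either on the form.

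The cost is a few sentences of protocol text, one reworded question and a short message to non-attenders. No new visits are needed. Recording work rises slightly and recorded event counts will be higher, which the report should explain as fuller ascertainment.

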### 2.8. Exercise Intensity Monitoring

Exercise intensity will be monitored using both objective and subjective measures. For an objective measure, participants will wear heart rate monitoring wristbands during all training sessions. Exercise intensity will be maintained at approximately 80–90% of estimated maximal heart rate (HRmax). While for subjective measure, participants will also rate their perceived exertion using the modified Borg Rating of Perceived Exertion (RPE) scale (0–10) immediately after each training session.

Given that the study involves participants with low prior physical activity levels, safety monitoring will be conducted throughout the intervention period. Before each training session, participants will be asked about their current physical condition, including any musculoskeletal pain, illness, dizziness, unusual fatigue, or other symptoms that may affect safe participation. During each session, the principal investigator or trained research personnel will observe participants for signs of exercise intolerance, including excessive breathlessness, dizziness, chest discomfort, nausea, musculoskeletal pain, or inability to maintain correct movement technique. Participants will be instructed to stop exercising immediately if they experience any concerning symptoms.

All adverse events and safety-related incidents will be documented using a standardized adverse event recording form. Information recorded will include the type of event, timing, severity, relationship to the intervention, action taken, and outcome. Serious adverse events, if any, will be reported to the research team and relevant ethics committee in accordance with institutional requirements.

